## Background

Life expectancy has been increasing in recent years. In parallel with the increase of life expectancy, the number of elderly patients undergoing surgery is rising. Some of the diseases, such as gastrointestinal cancers, are predominant diseases of this elderly population and the major causes of morbidity and mortality. It had been reported that more than 30% patients with gastric cancer were older than 70 years [1]. Age exceeding 70 years is an independent predictor of increased postoperative complications, in-hospital mortality, and longer hospital stays [2]. Among the postoperative complications, pulmonary complications are closely related to general anesthesia. Atelectasis develops within minutes after the induction of general anesthesia [3] and age is a risk factor of pulmonary complications. Almost all mechanically ventilated, elderly patients developed atelectasis and shunting during anesthesia [4].

Acupuncture is an integral part of an ancient Chinese system of medicine that has been used for more than 2500 years to treat diseases and relieve pain. The use of acupuncture during anesthesia, which is called anesthesia-assisted-anesthesia, is promising in three aspects [5–7]: decreasing the need for anesthetics such as opioids, alleviating adverse events, and exerting organ-protective effects. Electrical stimulation of acupoints, which includes electroacupuncture and transcutaneous electric acupoint stimulation (TEAS), was developed as an alternative to manual acupuncture. Electrical stimulation has several advantages over manual stimulation, such as causing less pain, being less time consuming, and with better standardization.

However, whether the more acupoints stimulated the better the benefit is still in debate. Though according to the Traditional Chinese Medicine (TCM) theory, combinative stimulation of acupoints is important, some investigators found that there was no difference between dual-acupoint and single-acupoint stimulation [8]. In this study, we hypothesize that TEAS before and during surgery would decrease the morbidity or mortality of major postoperative pulmonary complications at 30 days after gastrointestinal surgery in elderly patients, and dual-acupoint stimulation would be better than single-acupoint stimulation.

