### Design

We adhered to the Standard Protocol Items: Recommendations for Interventional Trials (SPIRIT) guidelines in the preparation of this protocol (see Fig. 1 and Additional file 1 for the SPIRIT Figure and Checklist, respectively). The trial is an investigator-initiated, multicenter, randomized clinical trial comparing treatment with dual-acupoint TEAS versus single-acupoint stimulation and no-stimulation before and during anesthesia in elderly patients undergoing gastrointestinal surgery. Three hundred and forty-five participants will be included from the following four hospitals: First Affiliated Hospital of Fourth Military Medical University (Xijing Hospital); Second Affiliated Hospital of Guangzhou University of TCM; First Affiliated Hospital of Chongqing Medical University; and First Affiliated Hospital of Zhengzhou University. These participants will be randomly assigned to three groups through central randomization in a 1:1:1 ratio. The central randomization system will be used and performed by the Department of Anesthesiology of Xijing Hospital. In each center, an investigator who is not involved in anesthesia and follow-up will perform the randomization. This investigator logs into the central randomization system and inputs the patient’s information, then a random number and group assignment will be immediately given by the system. According to the assignment, the patients will receive interventions from 30 min before anesthesia induction to the end of the surgery. The follow-up period lasts for 1 year. Outcomes are assessed at baseline and 1, 3, and 30 days, and 1 year after surgery.

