### Outcome measurement

*The primary outcome* is postoperative pulmonary complications occurring within 30 days after surgery.

Postoperative pulmonary events are scored on an ordinal scale of 1 to 4 (see supplementary material 3). A clinically significant postoperative pulmonary complication is defined as two or more items in the grade-2 complications or one item in the grade-3 or grade-4 complications.

*Secondary outcomes* include the incidence of postoperative pulmonary complications within 30 days after surgery; all-cause mortality within 30 days and 1 year after surgery; admission to the intensive care unit (ICU) and length of ICU stay within 30 days after surgery; the length of postoperative hospital stay; and medical costs during hospitalization after surgery.

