### Sample size calculation and statistical analysis

To calculate sample size, we used available data from the pilot study in our hospital on postoperative pulmonary complication incidence (unpublished). In the study, the incidence of postoperative pulmonary complications was 23% in the ST-36 TEAS group and 32% in the Control. Assuming an additional decrease by 9% in group DT (14%), with a power of 80% at the *P* = 0.05 level of statistical significance, 345 patients (*N* = 115 for each group) are needed.

Statistical analysis will be performed by the Department of Statistics of the Fourth Military Medical University. The statistician is blinded from the allocation of groups. SPSS19.0 statistical software packages will be used to analyze the data. Prior to all analyses, a detailed statistical analysis protocol was developed. The intention-to-treat (ITT) population was defined as the patients who are randomized and received at least one treatment session. The per-protocol (PP) population was defined as the patients who completed the study and did not have major protocol violations. All analyses were based on the ITT population and the PP population. The result of the ITT analysis will be compared with that of the PP analysis to check whether the results are consistent.

All data will be checked by two investigators. We compare postoperative variables with either Student’s *t* test or the Mann-Whitney *U* test for continuous variables, depending on the characteristics of the variables, and we use the *χ*^2^ test for categorical variables. We compare both the composite primary outcome of incidence of postoperative pulmonary complications within 30 days after surgery and the secondary outcome of occurrence of systemic inflammatory response syndrome (SIRS) complications by postoperative day 30 with an unadjusted *χ*^2^ test, weighting every individual complication equally. Comparison between the groups is made by analyzing data with the post-hoc method. Where appropriate, we express statistical uncertainty with 95% confidence intervals (CIs). We calculate Kaplan-Meier estimates of survival curves, and we use log-rank tests to compare survival distributions between study groups. We will censor data used for Kaplan-Meier estimates when patients do not have a postoperative pulmonary complication during the study period. Analyses are performed using SPSS 13.0 software and a two-sided *P* < 0.05 was considered statistically significant.

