We focus on a specific population though this trial is a pragmatic design. First, we exclude patients with severe comorbidities because, in these patients, the postoperative complications could be so severe that protection by TEAS will be too weak to be observed. Second, we exclude patients with contraindications to electrical stimulation, to ensure that TEAS would not do harm to these patients.

Based on TCM theory, the onset of acupuncture’s effect is 15–30 min, and acupuncture during anesthesia may be not comparable to that in conscious patients. Previous studies in which acupuncture was started after the induction of anesthesia revealed reduced efficacy or a lack of efficacy, although the mechanism underlying this phenomenon is not known [15, 16]. So in our study we will start the TEAS at 30 min before anesthesia induction.

Considering that among the postoperative complications, pulmonary complications are closely related to general anesthesia, we choose the incidence of pulmonary complications as primary outcome. Atelectasis develops within minutes after the induction of general anesthesia [4] and age is a risk factor for pulmonary complications. Age-related changes in pulmonary function [17] may increase the possibility of intraoperative lung injury. Almost all mechanically ventilated elderly patients developed atelectasis and shunt during anesthesia [5].

A limitation of this study is the validity of blinding, since interventions will begin when the participants are awake. To solve the problem, for all participants, we attached electrodes to all acupoints and the patients are told that they may or may not feel the stimulation. At the end of the follow-up, to evaluate participant blinding, the patients also are asked which of the groups they believed they belonged to and to give a reason for their choice. By these manipulations, we hope to blind the participants.

In conclusion, the results of this trial are expected to confirm whether this acupuncture-related technique is effective in decreasing postoperative complications in elderly patients.

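### The primary test is fixed as unadjusted although age, a named risk factor, and centre, the stratification factor, are known for every patient: a small, avoidable loss of precision

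*Protocol article*

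**What the plan says.** The primary outcome "is postoperative pulmonary complications occurring within 30 days after surgery" (Protocol article, Outcome measurement). Under Sample size calculation and statistical analysis, one sentence assigns the test for both this outcome and a systemic inflammatory response outcome: they are compared "by postoperative day 30 with an unadjusted" chi-square test. The quoted words follow the second outcome, but the sentence opens by naming both, so the choice governs the primary analysis. The article mentions no covariate-adjusted or centre-stratified analysis.

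On age, the Background says "Age exceeding 70 years is an independent predictor of increased postoperative complications, in-hospital mortality, and longer hospital stays", and the Discussion says "age is a risk factor for pulmonary complications". The inclusion criteria require age 65 or older, so age is recorded for everyone. Under Interventions and comparison, randomisation is stratified by study centre; the Design section lists four hospitals. No other stratification factor is given.

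**The concern.** The article identifies a predictor of its own primary endpoint, has it for every patient before randomisation, and then fixes a primary test that does not use it. The same test ignores the factor on which allocation was stratified. Adjusting for prespecified pre-randomisation variables is valid and usually gains some precision without recruiting anyone.

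This trial has little information to spare on part of its question. The Background hypothesis includes superiority of dual over single stimulation, a planned difference of 9 percentage points with 115 patients per arm. The word unadjusted is an explicit choice in the article and is not a detail left to the separate analysis document, which is not shown. A supportive adjusted analysis there would not alter the primary test fixed here.

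**Working it through.** **Inputs from the article.** Rates: "the incidence of postoperative pulmonary complications was 23% in the ST-36 TEAS group and 32% in the Control", and 14% assumed for the dual-acupoint arm (DT). The single-acupoint arm is ST. The sample is 345, or 115 per arm, planned "with a power of 80% at the" 0.05 level; the analysis is two-sided. The mean of the three rates is 23%.

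**Inputs that are assumptions.** The article gives no effect size for age and no age distribution. I take an odds ratio (OR) per 10 years of 1.3 to 2.5 and, with entry at 65, an age SD of 4.4 to 5.3 years.

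**Step 1: the plan's own figure.** With the pooled-variance formula for two proportions, 32% v 14% at two-sided 0.05 and 80% power needs 85 per arm. A figure close to 115 appears only with an adjustment that the article does not state: 114 per arm at alpha 0.05/3, where 115 gives power 0.808. The checks below use the stated 0.05.

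**Step 2: unadjusted power at n = 115 per arm.** Power = Φ{[|p1 − p2|√n − 1.96√(2p̄(1 − p̄))] / √(p1(1 − p1) + p2(1 − p2))}.

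- DT v Control: (0.18 × 10.724 − 1.96 × 0.595)/0.581 = 1.31, power 0.906.
- DT v ST: (0.09 × 10.724 − 1.96 × 0.549)/0.545 = −0.20, power 0.419.
- ST v Control: power 0.332.

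**Step 3: outcome variance explained by age (R²).** To a first approximation, R² ≈ p(1 − p) × (SD × ln OR / 10)².

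- Low end (OR 1.3, SD 4.4): 0.23 × 0.77 × (0.44 × 0.262)² = 0.0024.
- High end (OR 2.5, SD 5.3): 0.23 × 0.77 × (0.53 × 0.916)² = 0.042.

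Simulating the logistic risk model with a skewed age distribution from 65 upward gives slightly larger values: 0.3%, 0.6% and 2.0% for ORs of 1.3, 1.5 and 2.0 at SD 4.4, and 0.9%, 2.7% and 4.8% for ORs of 1.5, 2.0 and 2.5 at SD 5.3. The range is therefore about 0.3% to 5%.

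**Step 4: what that is worth.** Effective n per arm = 115/(1 − R²), put back into the Step 2 formula.

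| R² | Equivalent total | Extra patients | DT v Control | DT v ST | ST v Control |
|---|---|---|---|---|---|
| 0 | 345 | 0 | 0.906 | 0.419 | 0.332 |
| 0.003 | 346 | 1 | 0.906 | 0.420 | 0.333 |
| 0.02 | 352 | 7 | 0.911 | 0.426 | 0.338 |
| 0.05 | 363 | 18 | 0.919 | 0.437 | 0.347 |

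The largest gains are 1.3, 1.8 and 1.5 percentage points.

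**Step 5: check by simulation.** An unadjusted chi-square was compared with a logistic score test adjusted for age and four centres (30,000 runs, assumed centre SD 0.3 on the logit scale, age SD about 4.4). For DT v Control, power went from 0.912 to 0.916 at OR 1.5 and from 0.909 to 0.917 at OR 2. At OR 2, DT v ST went from 0.421 to 0.437 and ST v Control from 0.332 to 0.346. With no treatment effect (OR 1.5), rejection was 0.049 unadjusted and 0.052 adjusted, so both tests hold their level.

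**Step 6: can the model be fitted?** Expected events are 115 × (0.14 + 0.23 + 0.32) = 79. Two treatment terms, one age term and three centre terms make six coefficients, or about 13 events each.

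**The case against.** The strongest reply is that nothing here is wrong. Randomisation balances age in expectation, and the error rate of an unadjusted chi-square already allows for chance imbalance. The gain from age is small in a population restricted to 65 and over, and the weak contrasts are weak because of the sample size. All of this stands, and it limits the point to a matter of efficiency.

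Four stronger readings are tempting, and the article does not support them.

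- **Bias from age imbalance.** With an age SD of 5.3 years, the difference in mean age between two arms has an SD of 5.3 × √(2/115) = 0.7 years. At 23% risk and ORs of 1.5 to 2.5, that moves the risk difference by an SD of about 0.5 to 1.1 points. This is random error, already inside the test's standard error.
- **A baseline pulmonary covariate is available.** A reader might infer this from "Outcomes are assessed at baseline and 1, 3, and 30 days, and 1 year after surgery". The endpoint is a new postoperative event and has no usable baseline value, and the exclusion criteria remove preoperative pneumonia, ventilation and previous lung surgery. The article describes no preoperative lung measure, so gains that depend on one cannot be claimed.
- **Age is stated to predict the primary event independently.** The independent-predictor statement concerns age above 70 and postoperative complications in general. For pulmonary complications the article says only risk factor.
- **Adjustment repairs the power of the 9-point contrasts.** Even at an R² of 0.20, far beyond what age could give, DT v ST reaches 0.502 and ST v Control 0.400.

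**Conclusion.** The point holds as a modest improvement that the plan passes up. The primary test is valid, but it uses neither the one risk factor that the article names and has for every patient nor the factor used to stratify allocation. For age alone the loss is about 1 to 18 patients' worth of information on 345, and at most about 1 to 2 percentage points of power per contrast. Those figures rest on the assumed ORs (1.3 to 2.5 per 10 years) and age SD (4.4 to 5.3 years). Centre adds an unknown amount, because the article says nothing about how rates differ between hospitals. The case for the change is that it costs almost nothing. It should not be presented as a remedy for low power.

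**What to change.** State the primary analysis as a logistic regression of the 30-day pulmonary outcome on treatment (three levels), age as a continuous variable, and centre. From that model report the standardised risk difference with a 95% confidence interval for each pairwise contrast. This keeps the result on the scale of the planned 9- and 18-point differences and avoids the shift in meaning of an adjusted odds ratio. Keep the unadjusted chi-square as a supportive analysis.

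Add no baseline pulmonary covariate unless the case report form is shown to record one for all patients, including the 113 already recruited when the article was submitted.

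Fix the wording before unblinding, and preferably before the interim analysis at 173 participants, so that the choice cannot depend on results by arm. The cost is a wording amendment to the analysis plan. Because the article says that protocol and plan were approved by the central ethics committee, it would be handled as an amendment to an approved document. Age and centre need no new data.

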#### Blinding

All patients will never have been subjected to transcutaneous electrical stimulation treatment before. Patients were told that they may or may not be able to feel the electrical stimulation. The skin surface was sterilized by alcohol and electrodes were pasted to bilateral ST36 and BL13. The generator was connected by leads to two sterile electrodes with a pre-gelled contact surface (approximately 1.5 in. × 1.5 in.) by a specific investigator who is not involved in anesthesia and follow-up. Treatment assignments were concealed from patients, data collector, research staff, the statistician, and the Data and Safety Monitoring Committee. The stimulator is placed in an opaque box to keep the surgical team and the anesthetists blinded to group allocation. The patients and the staff on the wards are not informed during follow-up about the intervention received. An independent Data and Safety Monitoring Committee oversees the study conduct and reviews the blinded safety data. Unmasking will be done when a severe adverse event happens. The Committee consists of a surgeon, an intensive care unit (ICU) physician and an anesthesiologist who is not involved in the study. The members of the Steering Committee vouch for the accuracy and completeness of the data and analyses and the fidelity of the study to the protocol.

At the end of the follow-up, to evaluate participant blinding, the patients are asked which of the groups they believed they belonged to and to give a reason for their choice. No investigator has access to patient allocation and outcome data at the same time. All statistical analyses are performed with the intervention groups named A, B, and C, and the statistician is blinded to allocation.

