Interim analyses are performed after half the required participants had been enrolled (*n* = 173). If the Institutional Review Board thought it was no longer ethical to withhold TEAS from the patients in the non-acupoint and Control groups based on the results of the interim analysis with pulmonary complications as the endpoint, the study will be stopped.

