## Discussion

The result of this trial is expected to provide convincing evidence that TEAS is effective for improving postoperative outcomes in older patients undergoing gastrointestinal surgery, and that dual-acupoint TEAS is better than single-acupoint.

TEAS is an alternative technique to acupuncture. Compared with acupuncture, it is easier and safer for non-acupuncturists to use. The use of acupuncture-related techniques during anesthesia may benefit patients considerably, especially by decreasing anesthetic consumption and reducing adverse events [6–11]. We have used electroacupuncture in clinical settings and obtained positive results. In healthy volunteers, we proved that electroacupuncture could alleviate low-perfusion-induced cerebral dysfunction [12]. In both adult and pediatric patients undergoing cardiac surgery, we proved that TEAS could improve cardiac outcomes and shorten ICU stays [13, 14]. Based on these evidences, we speculated that TEAS pretreatment would activate the endogenous protective mechanism, and then protect patients against subsequent surgical stress. We believe that this intervention will reduce the subsequent incidence, duration, and severity of organ dysfunction, and further reduce the morbidity and mortality. However, whether the more acupoints stimulated the better the benefit is still not clear. According to the TCM theory, combinative stimulation of acupoints is important. But Alizadeh et al. found that there was no difference between dual-acupoint and single-acupoint stimulation for treating postoperative nausea and vomiting [8].

However, currently there is not enough evidence for acupuncture based on strict clinical trial of evidence-based medicine because of the poor quality of current studies, such as small sample size, no description of methods for randomization, no standardized acupuncture protocol which may lead to performance bias, and so on. In this trial, we used a central randomization, multicenter design, standardized acupuncture protocol, with a large sample size to ensure power. A major issue in planning the design of this trial is which control should be used. Since the primary consideration of this trial is to clarify whether TEAS is effective in reducing postoperative complications, we all agree that both a non-acupoint Control group and a no-stimulation Control group are needed.

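### The half-way look can stop the trial for benefit on judgement alone, with the final test still at 0.05 and a protected group that is not randomised, so the 5% error rate is not controlled

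*Protocol article*

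**What the plan says.** The last paragraph of the section Sample size calculation and statistical analysis places an interim analysis after half the patients (173) are enrolled. The endpoint is pulmonary complications, which is the primary outcome. The IRB decides, on whether it is still ethical to "withhold TEAS from the patients in the non-acupoint and Control groups"; if it thinks not, then "based on the results of the interim analysis with pulmonary complications as the endpoint, the study will be stopped". No threshold or boundary accompanies the rule.

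The same section sizes the trial "with a power of 80% at the *P* = 0.05 level of statistical significance", concludes that "345 patients (*N* = 115 for each group) are needed", and sets the final criterion: "a two-sided *P* < 0.05 was considered statistically significant". Nothing there allows for an earlier look.

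The arms are given under Design and under Interventions and comparison: dual-acupoint TEAS (DT), single-acupoint TEAS (ST) and a Control with electrodes attached but no current. No non-acupoint arm is randomised. The Discussion nevertheless says that "both a non-acupoint Control group and a no-stimulation Control group are needed".

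Under Blinding, an independent Data and Safety Monitoring Committee "oversees the study conduct and reviews the blinded safety data". No role in the efficacy comparison is described for it.

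**The concern.** A look that can end the trial for benefit gives chance a second opportunity to produce a positive result. If the final test then uses the whole 0.05, the total error exceeds 5% by an amount that depends on how readily the interim can stop. Here that readiness is a matter of opinion, so the excess is neither fixed nor bounded.

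The rule also cannot be applied literally. One of the two groups it protects does not exist, so a reader cannot tell whether the stop rests on DT v Control, ST v Control, both TEAS arms combined, or the three-group test.

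An early stop is a realistic prospect under the planned rates. It would affect the trial's second hypothesis, that dual stimulation is better than single, and it would tend to exaggerate the effect reported.

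**Working it through.** **Inputs** (all from the section Sample size calculation and statistical analysis): rates of 32% (Control), 23% (ST) and 14% (DT); 115 per arm; two-sided 0.05; 80% power; interim at 173 of 345. The information fraction is t = 173/345 = 0.501, or about 58 per arm.

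**1. Does the planned size allow for the look?**
- DT v Control, n = [1.96·√(2p̄q̄) + 0.842·√(p₁q₁ + p₂q₂)]² / (p₁ − p₂)² with p̄ = 0.23: (1.166 + 0.489)² / 0.18² gives 85 per arm.
- Three-group chi-square on 2 df: effect size w² = 2(0.09²)/(3 × 0.23 × 0.77) = 0.0305. This needs 316 patients, or 106 per arm after rounding up; 345 patients give 83.6% power.
- DT v Control at 0.05/3 gives 114 per arm, close to the plan's 115, but the article states no such split.

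None of these routes to 345 contains an allowance for an interim. Which one was used is a separate question and is not held against the plan here.

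**2. Type I error for one comparison.** The two test statistics have correlation √0.501 = 0.708. A stop for benefit is counted as a positive result.

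Total error = 1 − P(|Z₁| < c₁ and |Z₂| < 1.96)

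| Interim two-sided threshold | Total error, final test at 0.05 |
|---|---|
| 0.001 | 5.02% |
| 0.005 | 5.19% |
| 0.01 | 5.45% |
| 0.02 | 6.08% |
| 0.05 | 8.31% |

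If the interim can stop only for benefit at nominal 0.05, the total is 1 − P(Z₁ < 1.96 and |Z₂| < 1.96) = 6.7%.

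**3. Simulation with binomial counts** (58 then 115 per arm, 23% in every arm): 0.05 at both looks gives 8.5% for one pair and 8.4% for the three-group chi-square. A benefit-only interim gives 6.8% to 6.9% for one pair. The small differences from step 2 come from discrete counts.

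**4. What an early stop would do at 14/23/32%.**
- DT v Control has P < 0.05 at the interim in 65% of simulated trials. When it does, the mean observed difference is 22 points against a true 18.
- DT v ST power is 24.5% at 58 per arm and 42% at 115. The information falls to 58/115 = 50%.

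**5. Boundaries that repair it, at t = 0.501.**
- Haybittle-Peto (interim P < 0.001, final 0.05): total error 5.02% for one comparison and 5.02% to 5.05% for the simulated three-group test. Simulated power is 84.8%, practically the same as with no interim.
- O'Brien-Fleming: interim 0.0052, final 0.0480. Sample size inflation is 1.008, so 345 × 1.008 ≈ 348 patients.

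**The case against.** The strongest objection is that this is a condensed article. It mentions an approved statistical analysis plan and a detailed analysis protocol, neither of which is shown, and a numerical boundary could sit there. An unreduced final 0.05 is also no proof of error, since the Haybittle-Peto repair keeps it too. Both points stand as far as they go: the missing boundary alone would be weak, and so would the final 0.05 alone. What remains is what the article does fix, namely a stopping criterion that is expressly a judgement, combined with a full 0.05 at the end. Nor can an unseen plan remove the conflict over arms inside this text.

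Several stronger readings are tempting, and the documents do not support them:
- **That the error rate is 8% or more.** This assumes nominal 0.05 at both looks. The article gives no interim threshold, and its rule concerns benefit only.
- **That it reaches about 20%.** Counting any of three unadjusted pairwise tests over both looks does give 19.9%, but about 12.4% is already present at the final look alone. That part is a multiplicity question, not an effect of the interim.
- **That stopping removes most of the DT v ST information.** It removes about half, and that comparison is weak even at full size.
- **That many outcomes would be missing at the interim.** If 113 patients had been recruited between 8 October 2017 and 6 March 2018 (149 days), then 113/149 × 30 ≈ 23 of the 173 would lack day-30 data at an immediate cut. But the article says only that the analysis follows half enrolment; it does not prescribe an immediate cut.
- **That an IRB decision contradicts the monitoring committee's role.** An ethics body may judge whether withholding treatment remains ethical, and the committee is not barred from advising it. The routing is partly a matter of preference.

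**Conclusion.** The point holds in this form: a judgement-based stop for benefit on the primary endpoint, together with an unreduced final 0.05, leaves the stated 5% uncontrolled. For one comparison the error lies between about 5.0% (interim 0.001) and about 8.5% (0.05 at both looks), with 6.7% to 6.9% for a benefit-only interim at 0.05. These figures assume equal arms, outcomes complete for about 58 per arm at the interim, and a stop counted as a claim of efficacy. The actual value within the range cannot be read from the article.

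The conflict over the non-acupoint group needs no assumption. The interim rule and the Discussion both name it, the randomisation does not include it, and the driving comparison is therefore undefined. The timing of the data cut and the choice of deciding body are secondary.

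**What to change.** Amend the protocol and analysis plan before anyone sees the interim comparison. The article reported 113 recruited, so at that time the look still lay ahead.

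1. Name the comparison and test that drive the stop.
2. Set a boundary: two-sided P < 0.001 at the interim with the final test at 0.05, or O'Brien-Fleming at about 0.005 and 0.048.
3. Reconcile the groups named in the interim rule and in the Discussion with the three arms under Interventions and comparison.
4. Run the analysis when 173 patients have completed day 30.
5. Preferably, have the existing Data and Safety Monitoring Committee review the comparison and advise the IRB.

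The cost is a short amendment. The first boundary loses practically no power; the second needs about 348 patients instead of 345 to keep it. The real downside is that early stopping becomes harder.
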